-Vestische Children's and Youth Hospital Datteln, Germany-Pediatric Hematology/Oncology, Dortmund Hospital, Germany-Department of Pediatrics and Adolescent Medicine, University Hospital Essen, Germany-Pediatric Hematology/Oncology, University Hospital Cologne, GermanyThe Rhine-Ruhr metropolitan area is beneficial for the fact that there are many oncological centers in a very small area, so that the treatment team can drive to them and deliver bedside counseling and support in presence. By selecting a prospective, multicenter study design, two cohorts of parents of children with a diagnosis of cancer and one cohort of medical staff from the participating pediatric oncology departments can be included. Sociodemographic data will be collected from all cohorts, with particular emphasis on the educational level of the parents, to determine whether education influences responses in the surveys. While one parent cohort will receive CM counseling, the other will serve as a waitlist cohort to be offered the respective CM counseling after the outcome assessment. Group assignment will be non-randomized by starting with a control cohort followed by the intervention cohort. After being informed about the study during the initial visit by their treating physician and signing written informed consent, parent cohorts will receive standard questionnaires three weeks after study inclusion. For the parent control cohort, the CM counseling will take place after this outcome assessment, while the parent intervention cohort will receive CM counseling before. Outcomes will be compared between groups. Medical staff will be trained in CM counseling strategies and assessed before and after the CM training. Outcomes will be compared within this group. A summary of the study design can be found in Figure 1. The active study period of recruiting is scheduled from December 2022 to end of 2027. Since there are five participating centers and a small project team, the time invested to be able to include subjects in the study will be in relation to the effort involved. For the medical staff, 100 participants are considered an acceptable and desirable number. Traveling to the study centers and maintaining contact with parents requires resources. The sample size for the survey and consultation includes 50 participants, evenly divided into two cohorts of 25 individuals each. We also expect a dropout of 10%, as parents who find themselves in such a difficult situation might also turn away.

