**Figure 1 F1:**
[figure not shown]
Study flow chart with control and intervention group and an overview of processes that will run consecutively in each participating cancer centers individually.

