### Eligibility criteria

3.2

To be included in the study, participating parents must have reached the age of 18. Their children should be under 18 years of age. Both parents have to give written informed consent to participate in the study. Children who have already reached the age of 16 must give their written consent as well. All first-onset oncological diseases are considered eligible diagnoses and the children have to be undergoing conventional cancer treatment in one of the participating cancer centers. Parents who already have experience in dealing with CM can still be part of the study.

Medical staff will be eligible if they are employed in one of the participating study centers within the framework of pediatric oncology and provide written informed consent. Insufficient knowledge of German is considered an exclusion criterion for both parents and medical staff.

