## Outcomes

4

All participants will be asked about baseline social demographics. Data on pediatric cancer characteristic will be obtained from medical records. Both cohorts of parents receive one questionnaire each, while medical staff receive questionnaires twice, once before and once after the CM training (see Figure 2). The questionnaires refer to the objectives already mentioned above in the protocol.

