Effectiveness outcomes are analyzed by examining parental satisfaction with counseling, including clarity of information on complementary medicine (CM) and its safety, using the PS-CATE and SDM-Q-9 scales. Means and standard deviations are reported, and paired *t*-tests or Wilcoxon signed-rank tests are applied to compare satisfaction scores before and after the intervention. Changes in parents’ ability to make informed decisions are assessed through pre- and post-intervention scores on the SDM-Q-9. Changes in parental attitudes toward CM, as measured by the ABCAM, and perceptions of the benefits of potentially harmful CM procedures, as assessed with the I-CAM-R, are analyzed using paired t-tests for within-group comparisons. Between-group differences, such as those between intervention and baseline cohorts, are tested using independent t-tests or Mann–Whitney *U*-tests. For medical staff, training needs and perceived burden are assessed using Likert scales, while changes in knowledge, attitudes (CHBQ), and practices regarding CM are evaluated with paired *t*-tests. Subgroup analyses are performed to identify predictors of changes in these outcomes.

To ensure psychometric robustness, subscales of multi-faceted questionnaires are averaged into non-weighted indices by calculating the mean of individual items where applicable. Cronbach's alpha coefficients are computed to assess the internal consistency of scales. All statistical tests are exploratory and conducted at a significance level of alpha = 0.05, without adjustments for multiple testing. For significant changes, additional regression analyses are conducted to identify predictors of change in predefined outcomes such as satisfaction, attitudes, or decision-making ability. Qualitative data are analyzed using thematic content analysis to complement the quantitative findings. This comprehensive approach ensures a robust evaluation of the feasibility, acceptability, and effectiveness of the intervention while identifying potential areas for refinement.

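### The sequential, non-randomized parent cohorts are compared only by unadjusted tests, so measured case-mix differences could be read as counseling effects

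*Protocol article*

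**What the plan says.** Section 3.1 (Study setting and design) describes the allocation: "Group assignment will be non-randomized by starting with a control cohort followed by the intervention cohort". The cohorts differ in when counseling is given relative to the questionnaire: "For the parent control cohort, the CM counseling will take place after this outcome assessment, while the parent intervention cohort will receive CM counseling before". The questionnaire comes three weeks after inclusion. Section 4 (Outcomes) gives each parent cohort one questionnaire, so there is no earlier score for the same parent.

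The article collects variables on which the cohorts may differ. Sociodemographic data are gathered "with particular emphasis on the educational level of the parents, to determine whether education influences responses in the surveys". Section 4 adds: "Data on pediatric cancer characteristic will be obtained from medical records". Eligibility is broad: "All first-onset oncological diseases are considered eligible diagnoses" (Section 3.2). Center is known for every family.

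For the contrast itself, Section 4.6 says: "Between-group differences, such as those between intervention and baseline cohorts, are tested using independent t-tests", or Mann–Whitney tests. Center appears there only in the tests of session completion rates. Regression is reserved for significant changes and aims at predictors of change. Subgroup analyses serve to describe variability or find predictors.

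**The concern.** Without randomization, two groups recruited one after the other may differ in education, diagnosis or center mix. If those variables also affect the scores, an unadjusted mean difference combines the counseling effect with the case-mix difference, and its p-value and interval do not separate the two. The article itself raises education as a possible influence on the answers, but gives it no role in the cohort comparison.

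At stake are the four parental questions listed in Section 4.3: satisfaction with information, ability to decide, attitudes, and perceived stress. Because parents complete one questionnaire, the between-cohort contrast is the parental comparison that the data collection supports, and measured covariates are the only adjustment available. The planned regression does not fill the gap. It is reached only after a significant result, so a difference masked by case mix would never get there, and it is not described as adjusting the cohort difference.

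**Working it through.** **The plan's own figure.** There is none to reproduce. Section 4.6 sets 25 parents per cohort as a feasibility target, with no effect size, SD or power.

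**Inputs from the article.** n = 25 per cohort and alpha = 0.05 (Section 4.6); expected dropout 10% (Section 3.1). Two-sided testing is assumed, as the article does not state it.

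**Step 1: rejection rate under a case-mix shift.** Assume no counseling effect and a shift of b SD between cohorts from case mix alone. The t statistic then has 48 degrees of freedom and noncentrality b × sqrt(25/2) = 3.536 × b. The critical value is 2.011.

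| Assumed shift b (SD) | Noncentrality | Chance of a significant t-test |
|---|---|---|
| 0 | 0 | 5.0% |
| 0.1 | 0.354 | 6.4% |
| 0.25 | 0.884 | 13.9% |
| 0.4 | 1.414 | 28.3% |

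With 22 per cohort (25 × 0.9 = 22.5, rounded down) the last three rates become 6.2%, 12.8% and 25.4%.

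**Step 2: how such a shift could arise.** Take one binary covariate such as higher education. The shift is the prevalence difference times the outcome gap between its levels, in within-level SDs. All these inputs are assumptions. Each setting was simulated 8,000 times with 25 per cohort and no true effect.

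- 40% v 40%, gap 0.8 SD: no shift; 5.2% significant unadjusted, 4.8% adjusted.
- 40% v 60%, gap 0.8 SD: shift 0.20 × 0.8 = 0.16 (simulated 0.15); 7.8% unadjusted, 4.6% adjusted.
- 30% v 70%, gap 0.8 SD: shift 0.40 × 0.8 = 0.32; 18.2% unadjusted, 5.0% adjusted.

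A linear model with cohort and the covariate removes the part of the bias that the covariate carries.

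**Step 3: what adjustment costs.** The model was simulated 20,000 times per setting with five centers (4 terms), three education levels (2 terms, an assumption) and two diagnosis groups (1 term), with no systematic imbalance. Residual degrees of freedom fall from 48 to 48 − 7 = 41. Change in the true standard error of the cohort difference, against the unadjusted one:

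- Covariates explain 20% of variance: falls about 3% with 50 parents, and 1–2% with 44.
- They explain 10%: rises about 3–4%.
- They explain nothing: rises about 8–10%.

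The shortcut sqrt(1 − 0.20) = 0.894, an 11% reduction, leaves out the loss from fitting seven covariate terms to 50 people, so it does not apply here. Systematic imbalance would raise the standard error somewhat further.

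**The case against.** The strongest reply is that little depends on this contrast. The main objective is feasibility and acceptability, the parental comparisons are secondary, and all tests are labelled exploratory. Section 5.1 treats the questionnaire results as indicative only. The progression criteria in Section 4.5 rest on recruitment, retention, acceptability, session completion and data completeness, and effectiveness is left to a later randomized trial. This stands and lowers the stakes. It does not remove the confounding, which can change the direction of a difference as well as its size. Section 4.3 also speaks of testing hypotheses, and Section 4.6 presents the approach as a robust evaluation that includes effectiveness.

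A second reply is that covariate sets are commonly left to an analysis plan that is not shown. That would apply if the article were silent. It names the tests, however, and gives regression a different purpose.

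A reader might also infer that nothing keeps the center mix alike. The Figure 1 caption points partly the other way, since it describes "processes that will run consecutively in each participating cancer centers individually". If each center runs both phases, each contributes to both cohorts, which partly balances center. What can be said is that no number per center and cohort is stated, so equal shares are not guaranteed.

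Finally, a reader might infer that case mix will produce false positives at the higher rates shown. The documents give no basis for the size or direction of any shift, and small shifts do little harm: 0.1 SD moves 5.0% only to 6.4%.

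**Conclusion.** The point holds as a modest one. The cohorts are sequential and non-randomized, the named tests are unadjusted, and education, cancer characteristics and center are available but unused in that contrast. Measured case-mix differences could be read as counseling effects. The rates of about 6%, 14% and 28% rest on assumed shifts of 0.1, 0.25 and 0.4 SD, two-sided testing and 25 analyzed parents per cohort. They show sensitivity and do not estimate this study's error rate.

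Two stronger conclusions are not supported. Adjustment cannot be justified by precision, because the standard error changes little and may rise. Nor would adjustment make the comparison free of confounding: differences in calendar time between the cohorts, and unmeasured differences, would remain. Section 5.2 (Limitations) covers compliance, social desirability, generalizability and self-selection, but neither of these.

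**What to change.** In Section 4.6, make the main between-cohort analysis of each parental score a linear model of the three-week score on cohort plus a few pre-specified covariates: center, education coded coarsely, and broad diagnosis group. Report the adjusted difference with its 95% CI whether or not any test is significant, and keep the t-test or Mann–Whitney test as supportive. In Section 5.2, add that the cohorts are sequential and that calendar-time and unmeasured differences remain after adjustment.

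The cost is wording and a short model specification; no new data are needed. The named downside is precision: the standard error may rise by up to about 9% if the covariates are not prognostic and not systematically imbalanced, and somewhat more under systematic imbalance. The covariate list should therefore stay short. No per-center quota is needed. It would conflict with the plan in Section 4.6 to take all eligible families who do not decline at once, and it would alter recruitment, which is itself a feasibility outcome.

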## Discussion

5

The diagnosis of cancer almost always represents a life-changing moment for the affected patients and their families, which is accompanied by a serious change in life circumstances and the subsequent search for different therapeutic options (45). In this context, questions about CM therapies are often raised in families with a child suffering from cancer. Previous projects are based on the fact that the parents had to travel long distances to consult reputable or dubious therapists and incur additional financial costs. The aim of this project is to establish professional bedside counseling and support for parents in their main hospital. Our main focus is to improve care of children with cancer by providing the best possible support regarding CM therapies. For this purpose, the current evidence level regarding the most-used CM therapies in pediatric oncology will be addressed and parents can obtain information through multiple channels. This project should also substantiate that parents are less stressed and have to make less effort to get the information they need. In addition, we would like to show that the team members treating the patient also benefit from professional support so that they are less frequently confronted with questions they do not know the answers to and have at expertise available on site from with to get support.

### Strengths

5.1

The present study will assess the feasibility of integrating CM into pediatric oncology and should serve as a new model for considering CM in relation to conventional concepts. Further results of this prospective cohort study will provide information on the decision-making ability of parents as well as on the feasibility and barriers to CM counseling. At this point, it must be emphasized that the outcome measures of the questionnaires only provide a direction and must be considered in the overall concept. By carrying out all planned project steps, the practicability is tested at the same time as basic information for carrying out the study on a larger scale in the future is provided. In this way, possible future obstacles can be circumvented before implementation. In addition, analyses of staff data will highlight support needs and barriers related to CM training. The intention is that medical staff learn to apply CM methods more confidently and are able to respond individually to the needs of their patients or the patients’ parents in the future. In the future, training will enable pediatric oncologists to provide their cancer patients with evidence-based advice on the safe use of CM. This may bring about an improved standard of care by reducing side-effects of CM and improving adherence to cancer treatments.

Both patients and staff alike have to be supported directly in the respective center because families often cannot leave the hospital for several weeks and time-consuming trips to unexperienced therapists could be avoided. A particular challenge in this study is networking within the five participating centers. In order to establish and maintain personal contact, it is mandatory for the project members to regularly visit the individual study centers and maintain a close exchange of information, feedback and ideas. To address this challenge, adequate time for networking is planned, and continuous efforts are made to optimize communication. This involves focusing on the parents participating in the questionnaires and consultations, seeking positive feedback from the medical staff, and ultimately analyzing the questionnaires to determine if sufficient time was invested in exchanging information with other study centers.

### Limitations

5.2

A further task is to ensure the compliance of the parents as well as the medical staff. Parents whose children have cancer face an emotional challenge and may find it difficult to engage with the trial. Studies show that an informed patient influences treatment-related expectations and patient engagement (46, 47). In addition, the parents are already burdened with substantial documentation and paperwork related to conventional studies, consent forms, and various other requirements. For this reason, solid communication skills and authentic empathy are required on the part of project staff (48), and the project team has been specifically trained to meet these demands. At the same time, hospital staff have many patients and therefore little time for additional activities. Compliance and commitment of both groups is maintained through close, personal contact in the form of educational talks as well as the possibility of telephone feedback. In addition, counseling and support will take place on site at the respective facility and strengthen engagement.

A possible effect could be that participants tend to respond in a socially desirable way, knowing that the study deals with attitudes and acceptance towards CM. To minimize this bias, we will ensure anonymity, stress the absence of right or wrong answers, ask neutral questions, and include implicit honesty prompts. Additionally, indirect questioning techniques will be used where appropriate to reduce socially desirable responses. These measures aim to encourage participants to disclose their true opinions and behaviors. Furthermore, a generalization of the results of the evaluation to Germany as a whole may be limited, as five out of 62 study centers in Germany will participate (8%). With regard to the generalizability of the results of the evaluation, it should be mentioned that individuals who are interested in CM may be more likely than other to participate in the survey. However, it could also be useful for people who have a rather positive attitude towards CM to be informed about its safe use. The need to improve communication about CM in pediatric oncology is also underlined by other authors (48).
